#### Randomization

A stratified block randomization approach will be used to allocate participants into intervention groups. Participants will be stratified based on their playing position into three distinct strata: (1) defenders, (2) midfielders, and (3) forwards. Within each stratum, participants will be randomly assigned in a 1:1 ratio to either the HRW group or the placebo group using a fixed block randomization method. Randomization sequences will be generated using a robust randomization algorithm, as described by Tu and Benn [28], and implemented via a secure web-based allocation system.

Following participant selection and baseline assessment, each participant will receive either HRW or a placebo in visually identical plastic-aluminum packs, with group allocation determined by the pregenerated randomization code. This process ensures allocation concealment and maintains blinding throughout the study.

#### Blinding

A double-blind design will be implemented to minimize potential bias. The type of water (HRW or placebo) will be packaged identically, with only distinct batch numbers differentiating them. These batch numbers will be coded and maintained solely by the manufacturer, remaining undisclosed until after data collection and statistical analysis. Due to the physical properties of H_2_—being colorless, odorless, and tasteless—participants will be unable to distinguish between the HRW and placebo by sensory perception. Both the players and their coaches, as well as the researchers responsible for data collection and outcome assessment, will be blinded to group allocation throughout the study. This procedure ensures allocation concealment and maintains the integrity of the blinding across all phases of the trial.

#### Sample Size and Power Analysis

The sensitivity analysis was performed using G*Power (Version 3.1, Heinrich-Heine-Universität). Considering a type 1 error of 0.05 (α=.05) and a test power of 80% (β=.15), the calculated sample size for repeated measures (within and between interaction) is 22 participants with 11 in each group. Considering a 10% sample loss, a total of 24 participants will be recruited for the study.

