#### Statistical Analyses

Statistical analysis and data management will be undertaken using SPSS version 22.0 software (IBM Corp), using an α≤.05. The normality and homogeneity of all data will be verified with the Shapiro-Wilk and Levene tests. Mean and SD will be calculated for each outcome measure with a parametric distribution and medians and quartiles for data with a nonparametric distribution. A repeated-measures ANOVA with one random factor as subject, two fixed factors as type of water (HRW/placebo) and time (prematch; postmatch; and 24, 36, and 72 hours post match), and mutual interaction of water and time will be used to assess acute and residual fatigue. When a significant effect of time or water is observed, pairwise comparisons will be performed using Tukey post hoc test. η^2^_p_ was used as a measure of effect size for each analysis of variance, and values were interpreted as having a small effect (0.01≤η^2^_p_<0.06), medium effect (0.06≤η^2^_p_<0.14), and large effect (η^2^_p_≥0.14).

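### The sample-size paragraph states two incompatible powers (80% and β=.15) and ties neither to an effect size or outcome, so the power of 22 players cannot be interpreted or reproduced

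*Protocol article*

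**What the plan says.** All of this stands in the protocol article, under Sample Size and Power Analysis. The paragraph opens with "The sensitivity analysis was performed using G*Power". It then sets the error rates: "Considering a type 1 error of 0.05 (α=.05) and a test power of 80% (β=.15". The result is that "the calculated sample size for repeated measures (within and between interaction) is 22 participants with 11 in each group", and allowing for 10% loss the recruitment target is 24.

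The paragraph gives no effect size, outcome, correlation between repeated measurements or sphericity value. The only effect-size figures in the article are in Statistical Analyses, where "values were interpreted as having a small effect (0.01≤η^2^_p_<0.06), medium effect (0.06≤η^2^_p_<0.14), and large effect (η^2^_p_≥0.14". Those partial eta-squared bands classify results once they are in; nothing links them to the 22.

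Two design inputs can be taken from other sections. Randomization gives two arms: "participants will be randomly assigned in a 1:1 ratio to either the HRW group or the placebo group". Statistical Analyses lists five measurement occasions: "time (prematch; postmatch; and 24, 36, and 72 hours post match".

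**The concern.** Power and β are complements, so a reader who is given both expects them to sum to one. Here they sum to 0.95, and no other section says which was meant.

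The name of the analysis adds to the doubt. A sensitivity analysis fixes N and solves for the detectable effect. An a priori analysis fixes the effect and solves for N. The paragraph uses the first name and reports the second kind of result, without the effect that either would need.

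What is at stake is how a null result is read. As written, it could be reported as coming from a trial with 80% power or one with 85% power, for any effect and any of the measured outcomes (repeated sprint ability, countermovement jump, creatine kinase, soreness). Type I error and the estimates themselves are not affected.

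**Working it through.** **Step 1. The contradiction, which needs no assumption.**

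- Power = 1 − β.
- Stated power 0.80 gives β = 1 − 0.80 = 0.20.
- Stated β 0.15 gives power = 1 − 0.15 = 0.85.
- Gap: 0.85 − 0.80 = 0.05, or five percentage points.

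**Step 2. Trying to reproduce N=22.**

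Inputs from the document: α = .05; k = 2 groups, 1:1; within-between interaction in a repeated-measures ANOVA; m = 5 occasions (from Statistical Analyses, not from the sample-size paragraph).

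Inputs not in the document, and so assumed and varied: effect size f, correlation ρ between occasions, sphericity ε (set to 1 unless stated).

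Formulas for the noncentral F test:

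- λ = f²·N·m·ε/(1−ρ)
- df1 = (k−1)(m−1)ε
- df2 = (N−k)(m−1)ε
- Power = probability that a noncentral F with these degrees of freedom and noncentrality λ exceeds the central F critical value at α = .05.

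Worked case, N=22, f=0.25, ρ=0.5, ε=1: λ = 0.0625 × 22 × 5 / 0.5 = 13.75; df1 = 4; df2 = 20 × 4 = 80; power = .836.

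Because f, ρ and ε are missing, this does not reproduce the plan's figure. It shows only that one conventional input set is compatible with it.

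**Step 3. Which figure is the slip?**

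Smallest even N for each target, with m=5 and ε=1:

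| f | ρ | Power at N=22 | N for 80% | N for 85% |
|---|---|---|---|---|
| 0.25 | 0.50 | .836 | 22 | 24 |
| 0.26 | 0.50 | .867 | 20 | 22 |
| 0.25 | 0.55 | .877 | 20 | 22 |
| 0.28 | 0.40 | .854 | 20 | 22 |
| 0.20 | 0.70 | .862 | 20 | 22 |

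In the first row, power is .791 at N=20 and .872 at N=24, so 22 is the 80% answer. In the other four rows it is the 85% answer. A change of 0.01 in f, or of 0.05 in ρ, is enough to switch.

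**Step 4. How much the unstated inputs matter.**

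- N=22, f=0.25, ε=1: power is .678 at ρ=0.3 and .975 at ρ=0.7, a difference of about 30 points.
- N=22, f=0.25, ρ=0.5: power falls from .836 at ε=1 to .745 at ε=0.75.
- N=22, ε=1: the f detectable with 80% power is 0.284 at ρ=0.3, 0.240 at ρ=0.5, 0.186 at ρ=0.7 and 0.152 at ρ=0.8. For 85% power the values are 0.301, 0.254, 0.197 and 0.161.

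**The case against.** The strongest reply is that this is a one-character slip in a condensed article. Correlation and ε may well be recorded in a fuller protocol or analysis plan that is not shown, the sensitivity label is loose terminology, and nothing about allocation, outcomes or analysis depends on it. Much of that stands. The missing ρ and ε are secondary on their own, and the matter is one of wording. It does not remove the contradiction, which is a misstatement and not an omission. The missing effect size is also harder to excuse: N is presented as the result of a calculation, and a power figure without an effect has no meaning.

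A reader might go further and infer that 22 players fit 80% power and fall short of β=.15, so that β=.20 must be the intended value. The document does not support this. The inference holds at f=0.25 and ρ=0.5, but reverses at inputs barely different from those, where 22 is exactly what 85% power requires. Nor can N=22 be shown to be wrong.

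A reader might also judge the trial by a single-time-point comparison of 11 against 11, which needs a difference of about 1.26 SD for 80% power. That is not the test that was powered. The plan powers the within-between interaction, so this figure does not measure the problem.

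**Conclusion.** The point holds as an inconsistency in the stated power together with a power claim that refers to no effect. The certain part is five percentage points of nominal power, and it rests on nothing beyond power = 1 − β. Which of the two numbers is mistaken cannot be settled from the document. The N comparisons are illustrations that depend on assumed f, ρ and ε and on taking five occasions from the analysis section. The consequence lies in how a null result may be described. It does not show that the trial is too small.

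**What to change.** In Sample Size and Power Analysis:

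1. State the single pair actually entered in G*Power, either 80% with β=.20 or 85% with β=.15.
2. Confirm that 22 analysed players deliver that power under the inputs used. If they do not, restate the power that 22 does deliver.
3. Give the effect size f to which the power refers, the outcome it concerns, and the number of measurements, correlation and ε that were entered.
4. Call the run an a priori sample-size calculation.

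The cost is a few words and one re-run of the G*Power calculation. Depending on which figure was the slip, the stated power may stay as it is or be restated. No change to the number of players is proposed.

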### Data Collection

#### Preparation of HRW and Placebo

HRW was obtained in 420 mL plastic-aluminum packs with a gas-tight cap (Aquastamina-R, Nutristamina, Ostrava, Czech Republic). Chemical characteristics of the HRW and placebo were determined using the pH/Oxidation-Reduction Potential/temperature meter (AD14, Adwa Instruments, Szeged, Hungary). The concentration of the dissolved H_2_ was determined using the H_2_Blue reagent (H_2_ Sciences, Henderson, Nevada) using the manufacturer’s guidelines. HRW/placebo characteristics were as follows: pH=7.9/7.7; oxidation-reduction potential −652/+170 mV; and dissolved H_2_ concentration 1.2-1.4/0.0 ppm. The placebo was obtained from the HRW manufacturer and was produced similarly to Aquastamina-R and packed in the same packs.

The participants were instructed to consume three plastic-aluminum packs (1260 mL) 24 hours before the simulated match, two plastic-aluminum packs (840 mL) after finishing the prematch measurement, one plastic-aluminum pack (420 mL) during the first half, and two plastic-aluminum packs (840 mL) consumed after the postmatch measurement. A total of 3780 mL of water was saturated.

#### RSA Measurement

Participants will complete five 20 m sprints (approximately 3 seconds) departing every 20 seconds with an active recovery (walk back to start). Two seconds before starting each sprint, the participants will be asked to assume the start position. The electronic timing gates (Brower Timing Systems, Draper, Utah) will be set at the start line, after 5 m and 10 m, and at the finish line at 20 m, and always 0.70 m above the surface. According to Pyne et al’s [29] recommendations, 3 scores will be calculated for the total time as the sum of the 5 sprints.

#### CMJ Test and VAS Scale

The CMJ test will be performed on a hardwood indoor surface, commonly used in sports science settings to ensure consistency and reliability of performance measurements. Participants performed 5 jumps and will be instructed to maximize jump height and minimize ground contact time with indoor football shoes. Participants start from an upright standing position with their hands on their hips. The CMJ test will be performed on a mobile optical device, the OptoJump system (Microgate SRL, Italy). Participants will perform three repetitions with a 3-minute recovery; the best attempt will be used. The average height and reactive strength index will be calculated. Reactive strength index will be calculated as jump time divided by contact time [30].

The self-reported perceptual measure by the VAS will be applied to assess lower limb muscle pain [31]. The VAS will be applied just after the CMJ test on a horizontal 100 mm length line with the left and right ends of the line corresponding to “no soreness during repeated maximal jumps” and “most soreness ever experienced during repeated maximal jumps.”

#### HR and Activity Demands

HR will be continuously recorded in 1-second intervals during the simulated match and all training sessions using a Polar Team^2^Pro System (Polar Electro, Kempele, Finland), whereby participants will have HR monitors affixed to their chest and level with the xiphoid process. HR responses will be presented relative to each participant’s individualized maximum HR from laboratory measurements. Raw data from the HR monitors will be exported into Excel (v16.35; Microsoft Corporation). To express training impulse, Edwards summated HR zones (SHRZ) will be calculated as 
[figure not shown]
, where *t_i_* is time spent in 5 HR zones (zone 1: 50%-60% of HR_max_; zone 2: 60%-70% of HR_max_; zone 3: 70%-80% of HR_max_; zone 4: 80%-90% of HR_max_; zone 5: 90%-100% of HR_max_). The external load will be calculated as the total distance covered, high-intensity distance [32] as distance covered at a speed >14.4 km·h^−1^, and PlayerLoad as 

, where *a_y_* is the straight acceleration vector, *a_x_* is the side acceleration vector, and *a_z_* is the vertical acceleration vector.

#### Statistical Analyses

Statistical analysis and data management will be undertaken using SPSS version 22.0 software (IBM Corp), using an α≤.05. The normality and homogeneity of all data will be verified with the Shapiro-Wilk and Levene tests. Mean and SD will be calculated for each outcome measure with a parametric distribution and medians and quartiles for data with a nonparametric distribution. A repeated-measures ANOVA with one random factor as subject, two fixed factors as type of water (HRW/placebo) and time (prematch; postmatch; and 24, 36, and 72 hours post match), and mutual interaction of water and time will be used to assess acute and residual fatigue. When a significant effect of time or water is observed, pairwise comparisons will be performed using Tukey post hoc test. η^2^_p_ was used as a measure of effect size for each analysis of variance, and values were interpreted as having a small effect (0.01≤η^2^_p_<0.06), medium effect (0.06≤η^2^_p_<0.14), and large effect (η^2^_p_≥0.14).

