## Methods

### Study Aim

Recognizing the critical role of recovery during intermittent or RSA performance, the anti-fatigue effects of H_2_ and its impact on mitochondrial ATP synthesis support the hypothesis that acute pre-exercise HRW administration, compared with a placebo, may positively affect biochemical, perceptual, and neuromuscular performance variables during a 72-hour period after a simulated football match. This study aims to assess the impact of pre-exercise HRW administration compared with a placebo on biochemical, perceptual, and performance variables within 72 hours after a simulated football match. The specific aims are to assess the impact of pre-exercise HRW administration on acute neuromuscular performance decrement, the impact of pre-exercise HRW administration on acute muscle soreness and the CK levels of players, and the impact of pre-exercise HRW administration on residual muscle fatigue and duration of return to readiness to play.

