### Study Design

This study protocol was designed according to the 2023 SPIRIT (Standard Protocol Items: Recommendations for Interventional Trials) statement [27]. The experimental study will use a robust research design, adopting a randomized, placebo-controlled, double-blinded, parallel structure (see Figure 1 and Multimedia Appendix 1).

To ensure unbiased results, the administration of HRW and the placebo was randomized and counterbalanced. The investigation will be conducted over a carefully planned 2-week period on a grass football field. During the initial session, participants will be familiarized with the Team^2^Pro Polar suite (1.4.5 version) and briefed on the regulations governing a simulated football match. Before the first measured session, participants will be stratified based on their playing positions (defenders, midfielders, and forwards) and subsequently randomized into either the HRW or placebo groups. Neuromuscular performance will be assessed through measures including the 20-meter repeated sprint test and CMJ. Metabolic fatigue will be measured through CK levels and muscle soreness, as reported using a VAS. These assessments will occur at critical time points: during simulated match day (SMD) immediately post warm-up; directly following the simulated football match to detect acute fatigue; and immediately post warm-up at intervals of 24 (SMD + 1 day), 48 (SMD + 2 days), and 72 (SMD + 3 days) hours after training sessions to detect residual fatigue. The first measurement sessions will be systematically scheduled on Monday afternoons, allowing for a standardized 72-hour recovery period following the last training session. To enhance ecological validity, the simulated match was designed according to official football rules officiated by an experienced referee, comprising two 35-minute halves, with 11 players per team and no substitutions allowed. Regarding intensity regulation, all participants will be instructed to perform at match intensity, which will be monitored using heart rate (HR) data and rate of perceived exertion scores. These measures will indicate consistent physiological workload across participants, supporting the comparability of internal load responses. Environmental conditions (eg, temperature, lighting) will be held constant throughout all testing sessions to reduce external variability.

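### The prematch value is used only as a time level, so the water main effect and same-time comparisons are unadjusted for it and the interaction uses it inefficiently

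*Protocol article*

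**What the plan says.** All references are to the protocol article.

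- **Statistical Analyses.** The model has a random subject factor and "two fixed factors as type of water (HRW/placebo) and time (prematch; postmatch; and 24, 36, and 72 hours post match". It adds the interaction: "mutual interaction of water and time will be used to assess acute and residual fatigue". No covariate is named. The follow-up rule is: "When a significant effect of time or water is observed, pairwise comparisons will be performed using Tukey post hoc test". The interaction is not named as a trigger, and the pairs to be compared are not listed.
- **Study Design.** Outcomes are first measured "during simulated match day (SMD) immediately post warm-up; directly following the simulated football match to detect acute fatigue", and then on each of the three following days. The third post-match time is 48 hours here and 36 hours in Statistical Analyses. That needs correcting but does not affect this point.
- **Study Aim.** The first specific aim is "the impact of pre-exercise HRW administration on acute neuromuscular performance decrement". Residual fatigue and return to readiness form a separate aim.
- **Sample Size and Power Analysis.** "the calculated sample size for repeated measures (within and between interaction) is 22 participants with 11 in each group". No effect size or correlation is given.
- **Randomization** has players receive their water after a baseline assessment. **Preparation of HRW and Placebo** has three packs taken 24 hours before the match and the next two after the prematch measurement. If the baseline assessment is the prematch measurement, these two sections conflict.

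**The concern.** The aims concern what happens after the match relative to before it, and the trial already collects the prematch value. As one of five outcome levels, that value affects the three planned analyses differently.

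1. The water main effect averages the arms over all five times. An effect absent before the match is diluted, and stable differences between players stay in the error term.
2. Same-time comparisons of the arms, if they are among the post hoc pairs, carry any chance prematch gap unadjusted. A match is likely to produce a time effect, so the post hoc step is likely to be triggered.
3. The interaction does use prematch, but with the slope fixed at 1. Covariate adjustment is more precise at any correlation below 1, apart from the small cost of estimating the slope. The interaction also tests four contrasts at once.

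With 22 analysed players, a real effect could be missed, or a chance prematch gap could be read as an HRW effect on a later day.

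**Working it through.** **Inputs from the article.** 11 per arm, α = 0.05, five times, 1:1 allocation.

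**Assumptions, because the article gives no figures.** Unit SD at each time; compound symmetry with correlation ρ from 0.3 to 0.9; true effect d = 0.8 SD; no effect at prematch until step 5. Powers are from the noncentral F distribution with n/2 = 5.5. Simulation of the main effect, interaction and adjusted mean agreed to about 1 point.

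**1. The plan's own figure.** For the within-between interaction, λ = f²·N·m/(1−ρ) with df 4 and 4(N−2). With assumed f = 0.25 and ρ = 0.5, N = 22 gives λ = 0.0625 × 22 × 5/0.5 = 13.75 and power 84%; N = 20 gives λ = 12.5 and 79%. So 22 is the smallest even N reaching 80%. The article writes "a test power of 80% (β=.15"; β = 0.15 means 85%, which needs 24. The stated 22 is met under these assumed inputs but cannot be confirmed.

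**2. Dilution and imbalance.** The main effect estimates (0 + 4 × 0.8)/5 = 0.64 SD, or 4/5 of the post-match effect. The standard error of a prematch difference is √(2/11) = 0.43 SD, and P(|gap| > 0.5 SD) = 2[1 − Φ(0.5/0.426)] = 24%.

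**3. One time point.** Unadjusted: λ = 5.5 × 0.8² = 3.52, df 1, 20, power 43%. Adjusted: λ = 3.52/(1−ρ²) × 18/19, df 1, 19, where 18/19 is the cost of estimating the slope.
- ρ = 0.3: λ = 3.67, 44%
- ρ = 0.5: λ = 4.45, 52%
- ρ = 0.7: λ = 6.54, 68%

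**4. All post-match times, sustained effect.**
- Main effect: λ = 5.5 × 0.64²/[(1+4ρ)/5], df 1, 20. At ρ = 0.5, λ = 3.75.
- Interaction: λ = 5.5 × Σ(e−ē)²/(1−ρ), df 4, 80. Here Σ(e−ē)² = 0.64² + 4 × 0.16² = 0.512, so λ = 5.63 at ρ = 0.5.
- Joint adjusted test: the covariance given prematch is (1−ρ)(I+ρJ), so λ = 5.5 × 4 × 0.64/[(1−ρ)(1+4ρ)] × 18/19, df 4, 76. At ρ = 0.5, λ = 8.89.
- Adjusted mean of the four times (1 df): variance (1+3ρ)/4 − ρ², same 18/19 factor, df 1, 19.
- Unadjusted 1-df change (post-match mean minus prematch): variance (1+3ρ)/4 + 1 − 2ρ, df 1, 20.

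| ρ | Main effect | Interaction | Joint adjusted | Adjusted mean | Unadjusted change |
|---|---|---|---|---|---|
| 0.3 | 58% | 30% | 61% | 80% | 48% |
| 0.5 | 45% | 42% | 63% | 81% | 62% |
| 0.7 | 37% | 66% | 76% | 90% | 83% |
| 0.9 | 32% | 99% | 99% | 99.9% | 99.9% |

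For an acute-only effect (0.8 SD at postmatch, none later) at ρ = 0.5, the interaction has 42% and the joint adjusted test 41%. The adjusted mean has 11%: the averaged effect is 0.2 SD and λ = 5.5 × 0.04/0.375 × 18/19 = 0.56.

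**5. If water has already acted at prematch.** Let a fraction f of the effect be present there. The main effect keeps (4+f)/5 of it, the interaction 1−f and the adjusted estimate 1−ρf. Power at ρ = 0.5, sustained effect:

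| f | Main effect | Interaction | Adjusted mean |
|---|---|---|---|
| 0 | 45% | 42% | 81% |
| 0.25 | 50% | 24% | 70% |
| 0.5 | 55% | 13% | 57% |
| 1 | 63.5% | 5% | 29% |

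For one time point, f = 0.25 already removes the gain: λ = 5.5 × (0.8 × 0.875)²/0.75 × 18/19 = 3.40 against 3.52, power 42% against 43%.

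**The case against.** The planned analysis is a valid test under randomization and already contains a comparison referred to prematch. A reader might infer that all between-arm inference is exposed to chance prematch gaps. The article does not support that: the interaction compares changes over time, a stable difference between arms cancels in it, and it is the test behind the sample size. The exposure is limited to the main effect and same-time comparisons.

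A reader might also take the rise from 42% to 81% at ρ = 0.5 as the gain from the covariate. It is not. It also reflects moving from a 4-df to a 1-df test; an unadjusted 1-df change contrast already reaches 62%. Nor is the average generally better, since it has 11% against 42% for an acute-only effect, and the article keeps acute and residual aims apart.

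Finally, a reader might infer that adjustment can never do worse than the plan. As the intake schedule is written, prematch follows the first three packs. The adjusted estimate then keeps more of the effect than the interaction, but the unadjusted main effect can be more powerful when most of the effect is already present at prematch.

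These objections stand and limit the point. So does the absence of any stated ρ: one value is unlikely to suit sprint time, jump, CK and soreness alike. None of them removes the dilution, the unadjusted same-time comparisons, or the precision available from a value already collected.

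**Conclusion.** The point holds as an inexpensive improvement in efficiency and interpretation; the plan is not invalid. The main effect targets 4/5 of the post-match effect when there is none at prematch. It and same-time comparisons carry an imbalance with standard error 0.43 SD.

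Under compound symmetry, 0.8 SD and no prematch effect, adjustment adds 9 points of single-time power at ρ = 0.5 and 25 at ρ = 0.7. For a sustained effect, the joint adjusted test gains 21 and 10 points over the planned interaction. The joint-test gain is nil or negligible at ρ = 0.9 or for an acute-only effect. The dilution and the power gains depend on how much effect is already present at prematch, which the article's account of the timing leaves unsettled.

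**What to change.** First reconcile Randomization with Preparation of HRW and Placebo on whether the prematch measurement comes before or after the first intake. Then amend Statistical Analyses:

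- Take the four post-match values as the outcome in the same random-subject model, with water, time and water-by-time as fixed effects and the prematch value of that outcome as a covariate. For CK, put covariate and outcome on the same scale.
- Report the adjusted HRW-minus-placebo difference at postmatch for the acute aim and at each later time for the residual aim, with the 4-df joint test of water and water-by-time. Give the average over times as a summary only.
- Show prematch values by arm descriptively.
- If prematch follows the first intake, describe the estimate as the effect beyond any prematch difference, and state that it keeps 1−ρf of the full effect.

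The cost is a wording change, one covariate and one error df, with no new data, visits or players. The drawbacks are slightly lower power if ρ is near 0, and the loss in step 5 of the working if water has already acted by prematch.

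### The stated ANOVA omits playing position, the factor that stratifies randomisation, so the water main-effect test loses precision if position is prognostic

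*Protocol article*

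**What the plan says.** On allocation, the Randomization section states: "Participants will be stratified based on their playing position into three distinct strata". Allocation inside a stratum is described thus: "participants will be randomly assigned in a 1:1 ratio to either the HRW group or the placebo group using a fixed block randomization method". Study Design describes the same stratification.

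On analysis, the Statistical Analyses section specifies "A repeated-measures ANOVA with one random factor as subject", with "two fixed factors as type of water (HRW/placebo) and time", together with the water x time interaction. The list of terms is complete as written, and position is not on it. Time has five levels. (This section lists 36 hours where Study Design lists 48; the count is five either way.) A significant effect of time or of water leads to Tukey pairwise comparisons.

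On assumptions, the same section says: "The normality and homogeneity of all data will be verified with the Shapiro-Wilk and Levene tests". Sphericity is neither mentioned nor excluded.

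The Sample Size and Power Analysis section sizes the trial on the within-between interaction, with 22 players, 11 per group.

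**The concern.** Stratifying by position balances it across the arms, so position no longer adds to the random error of the difference between arms. A model without position still counts that variance as error when it estimates the standard error. The water test then behaves as though the difference were noisier than it is: the true type I error falls below 5% and power is lost. With about 22 players there is little precision to give away, and the stratification has already been paid for in the design.

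The second matter concerns the within-player tests. One random subject factor implies equal variances and equal correlations across the five times. Measurements spread over 72 hours around a fatiguing match may well depart from that. If they do and the ordinary F is used, the time and water x time tests reject a true null too often.

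**Working it through.** **What the article supplies.** Three strata, 1:1 allocation within each, 22 players analysed, five times, alpha .05. It gives no position effect, no covariance matrix and no epsilon, so there is no figure of the plan's own to reproduce on this point. Every size below rests on a stated assumption.

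**1. Water main effect with position omitted.** Let R² be the share of between-player variance explained by position, with position exactly balanced across arms. The reported standard error uses the full variance, while the actual variability of the difference uses the fraction (1 − R²).

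- Ratio of reported to actual SE = 1/√(1 − R²)
- Between-player degrees of freedom = 22 − 2 = 20, critical t = 2.086
- True type I error ≈ 2·P(t₂₀ > 2.086/√(1 − R²))

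| Assumed R² | SE ratio | Effective cut-off | Type I error |
|---|---|---|---|
| 10% | 1.054 | 2.20 | .040 |
| 20% | 1.118 | 2.33 | .030 |
| 30% | 1.195 | 2.49 | .022 |

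A null simulation (40,000 trials, 12 per arm as 4/4/4, within-player correlation 0.5) shows the same direction. With position shifts of ±0.5 SD that are constant over time, the water test rejects in 2.6% of trials without position in the model and 4.9% with it. With ±1 SD the figures are 0.4% and 4.8%.

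**2. Interaction with position omitted.** In the same simulations a time-constant shift leaves the water x time test at 5.0-5.2%, because the subject factor absorbs it. The test moves only when the position effect itself varies over time. In two assumed cases, with position differences of ±0.5 and ±1 SD at their peak and a time profile of 0, 1, 1, 0.5, 0, it rejects in 3.7% and 1.2% of trials. Fitting position x time returns it to 5.1% and 5.0%.

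**3. Compound symmetry.** Null simulation, 11 per arm, five times, 40,000 trials per row; percentages are rejections by the water x time test at nominal 5%.

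| Assumed covariance | Epsilon | Uncorrected F | Greenhouse-Geisser |
|---|---|---|---|
| Compound symmetry, 0.5 | 1.00 | 5.2% | 3.9% |
| Correlation 0.5, unequal SDs | 0.82 | 6.0% | 4.1% |
| AR(1) 0.5 | 0.81 | 6.4% | 4.4% |
| AR(1) 0.7 | 0.69 | 7.2% | 4.5% |
| AR(1) 0.9 | 0.58 | 8.0% | 4.6% |
| AR(1) 0.7, strongly unequal SDs | 0.50 | 8.7% | 4.8% |

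The water main effect stays at 4.9-5.1% throughout, so this mechanism does not touch it.

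**4. Degrees of freedom used by the fix, at 22 players.** Position has three levels and costs 2 between-player degrees of freedom: 20 − 2 = 18. Position x time costs 2 × 4 = 8 within-player degrees of freedom: 20 × 4 = 80 falls to 18 × 4 = 72.

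**The case against.** The trial is sized on the interaction, and a position effect that is constant over time does no harm there. The loss falls on the water main effect, which averages over all five times including prematch, and the error is in the safe direction: fewer false positives, at the price of power. All of this stands and limits the point. It does not remove it, because the plan itself uses the water effect to trigger post hoc comparisons, and because the model is written out term by term, so the omission of position is stated and not inferred from silence.

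On sphericity, a condensed article may leave the correction to a fuller plan. That also stands. A reader might infer that no sphericity correction will be applied, but the Statistical Analyses section never says that the uncorrected F will be reported. What can be said is that the model as written implies compound symmetry and that neither Shapiro-Wilk nor Levene examines it.

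A reader might also infer that creatine kinase will be analysed on the raw scale. The article names no scale for it and neither plans nor excludes a transformation. Its remark on nonparametric distributions is a conditional rule for summaries. That inference is not supported.

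**Conclusion.** The mismatch between design and model is established by the article's own text. Its size is conditional. For 10-30% of between-player variance explained by position, with balanced arms, the SE of the water effect is about 5-20% too large and its type I error about .040 to .022. If position explains nothing, nothing is lost. The interaction is affected only by position effects that change over recovery.

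The sphericity point is secondary and doubly conditional: it requires that epsilon is below 1 and that the F is reported uncorrected. The interaction test then rejects a true null in about 6-9% of trials for epsilon 0.8 to 0.5, and there is essentially no inflation at epsilon 1.

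It would be tempting to say that the analysis is wrong in both directions at once. The documents do not support that. The two mechanisms act on different tests, water being conservative in the one case and time and water x time liberal in the other, and neither error is shown to occur with this trial's data. The position omission merits a change to the plan; the sphericity handling merits a clarifying sentence.

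**What to change.** Add playing position as a fixed factor in the repeated-measures model for every outcome. Add position x time where position effects are expected to vary over recovery, and decide this before unblinding. State that the Greenhouse-Geisser corrected F is the reported test for time and water x time.

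These are changes of wording only. Position takes 2 of 20 between-player degrees of freedom, and position x time a further 8 of 80 within-player degrees of freedom. The corrected F is slightly strict: in the simulations above it rejects in 3.9-4.8% of null trials, which costs a little power if sphericity does hold.
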